The secondary outcome will be the proportion of patients who reach HbA1c <7% without severe hypoglycemia (unrecoverable hypoglycemia without the help of others) at weeks 12 and 24. Other secondary outcomes include mean fasting blood glucose values for three consecutive days prior to weeks 12 and 24; levels of HbA1c at weeks 12 and 24; the proportion of patients having hypoglycemia (total, asymptomatic, daytime, nighttime, severe hypoglycemia, and coma/convulsions) at weeks 12 and 24; the number of steps taken during weeks 1–12 and weeks 13–24; recorded exchange unit by food group (grain, fish, vegetable, fat, milk, and fruit groups) in each breakfast, lunch, and dinner on 3-day food diary at weeks 12 and 24; daily insulin dose, body weight, and blood pressure at weeks 12 and 24; lipid profiles including total cholesterol, high-density lipoprotein (HDL) cholesterol, triglycerides, and low-density lipoprotein (LDL) cholesterol at weeks 12 and 24; body composition, including lean body mass and fat mass, at weeks 12 and 24; satisfaction evaluation by Diabetes Treatment Satisfaction Questionnaire (DTSQ) [13–16] and a questionnaire for ICT-based centralized clinical trial monitoring at weeks 12 and 24; the number of self-monitoring blood glucose measurements; the mean duration of medical consultations by doctors at the outpatient clinic; and the number and mean duration of telephone counselling by diabetes educators at weeks 12 and 24.

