### Anthropometric and vital sign measurements

At visits 1, 3, and 4, height, body weight, blood pressure, and pulse will be measured, and a brief physical examination will be performed. Body composition examination will be performed by bioelectrical impedance analysis (Table 1).

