### Laboratory tests

At visits 1, 3, and 4, blood samples are collected after at least 8 h of fasting to determine fasting glucose, HbA1c, white blood cell count (WBC), hemoglobin, hematocrit, platelet count, total protein, albumin, globulin, blood urine nitrogen (BUN), creatinine, uric acid, total bilirubin, aspartate aminotransferase (AST), alanine transaminase (ALT), alkaline phosphatase (ALP), calcium, phosphate, total cholesterol, triglycerides, HDL cholesterol, and LDL cholesterol. At visit 1, a urine hCG test is performed as a pregnancy test in women with childbearing potential.

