### Questionnaire for satisfaction with diabetes treatment and ICT-based centralized monitoring system

Subjects complete the DTSQ and the satisfaction questionnaire for the ICT-based centralized monitoring system to assess the impact of the intervention on the self-management of diabetes at visits 1, 3, and 4 [Additional file 2]. As the DTSQ has 2 versions, one assessing current status (DTSQs) and one assessing change (DTSQc), the DTSQs will be used at baseline (visit 1), visit 3, and endpoint (visit 4), and the DTSQc will be used at endpoint (visit 4).

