### Data analysis

All continuous variables will be presented as mean ± standard deviation, and categorical variables will be presented as frequency and proportion. For analyzing primary outcomes, the percentage of patients who reached the optimal insulin dose within 12 weeks is presented, and the difference between the two groups is compared using Pearson’s chi-square test or Fisher’s exact test if the frequency is low (<5). Differences are analyzed using Pearson’s chi-square test or Fisher’s exact test for categorical variables and Student’s t-test or Wilcoxon’s rank-sum test for continuous variables of secondary outcome variables. Comparisons between the two groups will be performed using a stratification analysis based on the use of pre-prandial insulin two or more times per day and each research institute. Prespecified subgroup analyses, including use of immunosuppressants (including steroids); type of DM; HbA1c >9%; use of pre-prandial insulin; aged over 65, 60, or 55; type of basal insulin; and stage of chronic kidney disease at baseline are performed. For handling missing data, last-observation-carried-forward (LOCF) imputation method would be performed.

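### Continuous secondary outcomes with a visit 1 value are compared without baseline adjustment, which gives up precision that the collected data could supply

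*Protocol article*

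**What the plan says.** The Data analysis section assigns continuous secondary outcomes to "Student’s t-test or Wilcoxon’s rank-sum test for continuous variables of secondary outcome variables". It names no baseline covariate and no change score. It then adds: "Comparisons between the two groups will be performed using a stratification analysis", with pre-prandial insulin use (two or more times per day) and research institute as the strata. These are the two factors that stratify the randomisation.

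Outcome variables lists the continuous outcomes as values at the follow-up visits, for example "levels of HbA1c at weeks 12 and 24".

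Baseline values of many of these outcomes are collected:

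- Laboratory tests: "At visits 1, 3, and 4, blood samples are collected after at least 8 h of fasting to determine fasting glucose, HbA1c", and lipids in the same list.
- Anthropometric and vital sign measurements: "At visits 1, 3, and 4, height, body weight, blood pressure, and pulse will be measured". Body composition by bioelectrical impedance is described in the same section.
- The questionnaire section schedules the status version of the DTSQ at visits 1, 3 and 4.

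Other continuous outcomes have no visit 1 value. Step count is defined as "the number of steps taken during weeks 1–12 and weeks 13–24", and the food diary is kept only before visits 3 and 4. Consultation time, telephone counselling and the number of glucose self-measurements arise during follow-up.

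**The concern.** The secondary hypothesis is better glycometabolic control in the ICT-based group. The sample is small and mixes type 1, type 2 and post-transplant diabetes, so patients are likely to differ widely in HbA1c, weight and lipids before treatment starts. Randomisation is stratified by site and pre-prandial insulin use, not by any of these baseline values.

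A two-sample test on the follow-up value leaves all of that between-patient spread in the error term. Where baseline predicts follow-up, adjustment removes part of it. At stake is the chance of detecting a real effect on these outcomes and the width of any interval reported for them.

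**Working it through.** **The plan's own figure.** The only computed size is for the binary primary outcome: 88% against 55%, two-sided alpha 0.05, power 90%. With pooled variance and mean proportion 0.715:

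n = [1.960 × √(2 × 0.715 × 0.285) + 1.2816 × √(0.88 × 0.12 + 0.55 × 0.45)]² / 0.33² = (1.251 + 0.762)² / 0.1089 = 37.2, so 38 per group.

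Dropout: 38 / 0.8 = 47.5, so 48 per group. Both figures reproduce. The article gives no calculation for continuous outcomes.

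**Inputs for the check.** The group size n = 38 (after dropout) and n = 48 (as recruited) come from Sample size assumptions. The SD and the correlation r between baseline and follow-up are not in the article. Results are therefore in SD units, and r is an assumption shown over a range.

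**Formulas** (95% CI half-width for the difference in means, N = 2n):

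- t-test on the follow-up value: t(N − 2) × √(2/n)
- ANCOVA on baseline: t(N − 3) × √(2/n) × √(1 − r²) × √(1 + 1/(N − 4)), where the last factor is the small cost of estimating the slope
- t-test on change, equal SDs assumed: t(N − 2) × √(2/n) × √(2(1 − r))

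For n = 38, √(2/38) = 0.2294. Unadjusted: 1.993 × 0.2294 = 0.457. ANCOVA at r = 0.5: 1.993 × 0.2294 × 0.866 × 1.0069 = 0.399. Ratios below are from unrounded values.

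| r (assumed) | Unadjusted, n = 38 | ANCOVA, n = 38 | Unadjusted relative to ANCOVA | Unadjusted, n = 48 | ANCOVA, n = 48 |
|---|---|---|---|---|---|
| 0 | 0.457 | 0.460 | 0.7% narrower | 0.405 | 0.408 |
| 0.3 | 0.457 | 0.439 | 4% wider | 0.405 | 0.389 |
| 0.5 | 0.457 | 0.399 | 15% wider | 0.405 | 0.353 |
| 0.7 | 0.457 | 0.329 | 39% wider | 0.405 | 0.291 |

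**Equivalent sample size.** An unadjusted test matches ANCOVA on 38 per group only with 38/(1 − r²) per group: 41.8, 50.7 and 74.5 at r = 0.3, 0.5 and 0.7.

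**Power** for an assumed difference of 0.5 SD, n = 38, normal approximation: Φ(0.5 / (0.2294 × √(1 − r²)) − 1.960).

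- Unadjusted: Φ(2.179 − 1.960) = 59%
- Adjusted, r = 0.3: Φ(2.285 − 1.960) = 63%
- Adjusted, r = 0.5: Φ(2.517 − 1.960) = 71%
- Adjusted, r = 0.7: Φ(3.052 − 1.960) = 86%

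**If change scores were meant.** Half-widths at n = 38 would be 0.541, 0.457 and 0.354 at r = 0.3, 0.5 and 0.7, which is 23%, 15% and 8% wider than ANCOVA.

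The figures concern the t-test. The rank-sum test also ignores baseline; its loss was not calculated. The ANCOVA figures adjust for baseline only. Site and insulin stratum, two levels each, would use one further degree of freedom apiece.

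**The case against.** The strongest reply is that nothing here is invalid. Under randomisation a two-sample test is unbiased, and its standard error already allows for chance baseline differences. That stands: the loss is one of efficiency, not bias. The primary outcome is binary, and neither it nor its sample size is touched.

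A second reply is that the article does not say outright whether follow-up values or changes are tested, and that covariates for secondary outcomes are often settled in an analysis plan. The first half is fair, but the listed outcomes are values at weeks 12 and 24, and even a change-score test is less precise than ANCOVA at every r shown. As to the second, the article does not leave the method open: it names the tests.

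Third, the gain is unknown. Entry requires HbA1c of at least 8.0%, and restricting the range in this way tends to lower r, so a moderate r for HbA1c cannot be taken for granted. This also stands, and is why a range is given. The gain should be larger for stable traits such as weight.

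A reader might go further in three ways that the documents do not support:

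- That every continuous secondary outcome loses precision. Steps, food exchange units, consultation and telephone measures and self-measurement counts have no visit 1 value. The fasting glucose outcome is a three-day mean before weeks 12 and 24, and the article does not show that a matching baseline is collected at visit 1. Nor does the Data analysis section announce confidence intervals, so the loss falls on the tests as well as on any interval reported.
- That the stratification factors are ignored. The Data analysis section announces an analysis stratified on both.
- That adjustment makes last-observation-carried-forward unnecessary. ANCOVA at each visit does not deal with missing visits, and the imputation sentence is not confined to continuous outcomes.

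**Conclusion.** The point holds for HbA1c, lipids, body weight, blood pressure, lean and fat mass and the DTSQ status version. The planned tests for these are valid but do not use a pre-randomisation value that is already collected, and the site and insulin strata do not stand in for it. The loss ranges from nothing when r is near 0 to an interval about 39% wider at r = 0.7, with a corresponding drop in power from 86% to 59% for a 0.5 SD difference. These sizes rest on assumed values of r and of the difference, and on 38 evaluable patients per group. Because adjustment costs under 1% when baseline carries no information, the case for it does not depend on which r is correct. It is a worthwhile improvement to the secondary analyses, not a threat to the trial's main conclusion.

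**What to change.** For the outcomes named in the verdict, make the main comparison an ANCOVA at week 12 and at week 24, or one repeated-measures mixed model over both visits, with the visit 1 value, site and pre-prandial insulin stratum as covariates. Report the adjusted mean difference with its 95% CI. State in advance the scale on which skewed variables will be analysed. Keep the named two-sample tests for continuous outcomes without a visit 1 value, and leave the primary analysis as it is. Handling of missing data needs its own statement and is not settled by this change.

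The cost is a change of wording in the analysis section and slightly more programming. No extra measurement, visit or patient is required.

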### Outcome variables

The primary outcome will be the proportion of patients who reach the optimal insulin dose within 12 weeks of enrolling in the study, without severe hypoglycemia or unscheduled visits to the clinic. Achievement of the optimal insulin dose is defined as follows: A. For a patient who uses basal insulin only or basal insulin with pre-meal rapid-acting insulin once per day, 1) three or more fasting blood glucose values within the target range (80 to 130 mg/dL or 100 to 140 mg/dL) during week 12 (last 7 days prior to visit 3), 2) no nocturnal (from 11 pm to 7 am) or pre-breakfast hypoglycemia (<70 mg/dL) during week 12, and 3) variation of basal insulin dose (defined as the difference between the highest and lowest basal insulin doses) <10% of the mean total basal insulin dose during week 12. B. For a patient who uses multiple daily injections, including basal insulin with pre-meal rapid-acting insulin at least twice per day, the criteria are those in A plus 4) three or more days in which the correction dose of pre-meal insulin is required less than three times per day during week 12, and 5) no daytime (from 7 am to 11 pm) hypoglycemia (<70 mg/dL) during week 12.

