### Sample size assumptions

In a previous study that utilized mobile phones for insulin titration intervention for subjects with type 2 diabetes, proportions of patients reaching optimal insulin dose within 12 weeks were 88% and 37% in the intervention and usual care arms, respectively [7]. In the present clinical trial, for both the intervention and control groups, we provide telephone counseling 1 week after patient education and allow telephone counseling if the blood glucose level does not meet the target level in both ICT-based intervention and conventional intervention groups. Therefore, the rate of reaching the primary endpoint of the control group is expected to be 55%, higher than that of the reference, and the estimated proportion of the intervention group that meets optimal insulin dose is 88%, which is similar to the reference. With these assumptions, a sample size of 38 subjects per group is needed with a two-sided alpha threshold of 0.05 with 90% power. We aimed to recruit 96 participants (48 per group) to allow for a dropout rate of 20% during follow-up (Samsung Medical Center, *n* = 76; Samsung Changwon Hospital, *n* = 20) [17].

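### LOCF is the stated rule for missing data, but the primary outcome is defined only on week 12, so the rule can score the same patient as a success or a failure

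*Protocol article*

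**What the plan says.** All references are to the protocol article.

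- **Data analysis.** The section opens with the primary comparison (Pearson's chi-square or Fisher's exact test) and closes with: "For handling missing data, last-observation-carried-forward (LOCF) imputation method would be performed". No endpoint is excluded, no other missing-data rule appears, and the level at which values are carried is not given.
- **Outcome variables.** The primary outcome is "the proportion of patients who reach the optimal insulin dose within 12 weeks of enrolling in the study, without severe hypoglycemia or unscheduled visits". Every optimal-dose criterion refers to week 12, meaning the "last 7 days prior to visit 3":
  - Criterion 1 asks for "three or more fasting blood glucose values within the target range (80 to 130 mg/dL or 100 to 140 mg/dL) during week 12".
  - Criterion 2: no nocturnal hypoglycemia and no "pre-breakfast hypoglycemia (<70 mg/dL) during week 12".
  - Criterion 3: "variation of basal insulin dose (defined as the difference between the highest and lowest basal insulin doses) <10" per cent of the mean total basal dose.
  - Criteria 4 and 5, for multiple daily injections only: at least three days with fewer than three pre-meal corrections, and no daytime hypoglycemia.
- **Study design.** Assessments are scheduled at baseline, week 12 and week 24.
- **Sample size assumptions.** The plan assumes 88% against 55%, 38 per group for 90% power at two-sided 0.05, and 48 per group "to allow for a dropout rate of 20% during follow-up".

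**The concern.** LOCF needs an earlier value of the same variable. The composite has none after baseline. What exists before week 12 is a stream of home glucose readings and recorded doses. Filling week 12 from that stream creates constant values, and constancy is much of what the endpoint tests: a stable basal dose and no hypoglycemia. A completer has to show this over a real week, whereas a patient who stopped recording would be credited with it.

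Both readings are consistent with the sentence as written, and they can give opposite answers for the same patient. At stake is the primary status of every patient without adequate week-12 records. Their number may also differ by arm, because the section on the ICT-based intervention group describes educator calls when records are missing after a feedback message, and no matching follow-up is described for the conventional arm.

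**Working it through.** **1. The plan's own sample size.** With p₁ = 0.88, p₂ = 0.55 and mean 0.715, the pooled-variance formula is

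n = [1.96·√(2·0.715·0.285) + 1.2816·√(0.88·0.12 + 0.55·0.45)]² / 0.33² = (1.251 + 0.762)² / 0.1089 ≈ 37.2, so 38 per group.

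Dropout: 38 / (1 − 0.20) = 47.5, so 48. Both figures reproduce; the sample size is not in error. The allowance is 48 − 38 = 10 patients per arm.

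**2. The rule applied to the composite.** There is no scheduled value between baseline and week 12. Either LOCF cannot be applied, or baseline is carried and the patient is a failure.

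**3. The rule applied to home records.** As an illustration, carry one fasting value of 120 mg/dL and one basal dose of 20 units across 7 days.

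| Criterion | Carried week | Met? |
|---|---|---|
| 1: at least 3 fasting values in 80–130 | 7 of 7 | yes |
| 2: no value below 70 at night or before breakfast | none | yes |
| 3: dose range under 10% of mean | 0 against a limit of 2 units | yes |
| 4 (multiple injections): at least 3 days with fewer than 3 corrections | 7 of 7 if the carried day had fewer than 3 | yes, on that condition |
| 5 (multiple injections): no daytime value below 70 | none if the carried value is at least 70 | yes, on that condition |

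The gain is not on criterion 1. If each reading is in range independently with chance 0.5, a real week of seven readings gives three or more with probability 0.773, against 0.5 for one carried reading. At 0.3 the figures are 0.353 and 0.3. The gain is on criteria 2, 3 and 5, where a constant acceptable value passes automatically.

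**4. How far classification can move the result.** Illustrative completer successes are 33/38 and 21/38 (close to 88% and 55%), with 10 patients per arm missing; Pearson's chi-square.

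| Missing patients scored as | ICT v conventional | p |
|---|---|---|
| failures in both arms | 33/48 v 21/48 | 0.014 |
| successes in both arms | 43/48 v 31/48 | 0.004 |
| failures in ICT, successes in conventional | 33/48 v 31/48 | 0.67 |

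The last row is an extreme, not an expectation.

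**5. Unequal missingness with no true difference among completers.** Assume 70% success among completers in both arms, and 10% missing in the ICT arm against 30% in the conventional arm. None of these figures is in the plan. If a missing patient is scored a success with probability q,

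difference = (0.63 + 0.1q) − (0.49 + 0.3q) = 0.14 − 0.2q.

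This gives +14 points at q = 0, +8 at q = 0.3, +2 at q = 0.6 and −6 at q = 1. With equal missingness and equal q, the difference under the null is zero.

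**6. Power if missing counts as not reached.** If 88% and 55% are completer rates and 20% per arm are missing: 0.8·0.88 = 70.4% and 0.8·0.55 = 44.0%, a difference of 26.4 points. Power at 48 per arm is about 75%; 90% would take about 72 per arm.

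**The case against.** The LOCF sentence is general, does not name the primary outcome, and may be refined in an analysis plan that is not shown. Carrying scheduled visits only would not manufacture successes. That is fair as far as the level of imputation goes. It does not rescue the rule, because on the visit-level reading there is no post-baseline composite to carry. The point is a stated rule that does not fit the endpoint, not a missing detail.

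Several stronger readings are tempting but not supported:

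- **A single in-range reading makes a dropout a full success.** A basal dose must be carried too, and a correction count for multiple injections. Severe hypoglycemia and unscheduled visits are not confined to week 12, so a patient with either one earlier still fails.
- **The coding rule swings the result by 20 points.** That compares all missing patients as successes with all as failures (−6 to +14 in step 5). With a carried-forward success chance of 0.3 to 0.6, itself an assumption, the range is +2 to +8.
- **Recording is checked only in the ICT arm.** The section on data acquisition and evaluation has the coordinator check synchronization and transmitted data in both arms before weeks 12 and 24. Hypoglycemia and insulin dose are also taken by interview at those visits. What is described for the ICT arm alone is the ongoing educator follow-up of missing records.
- **Ten patients per arm are expected to be affected.** The 20% covers the whole 24-week follow-up, so 10 is the figure only if all dropout precedes week 12. Patients who stay in the trial but record too little that week would come on top.

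One further objection stands: counting missing as failure is not neutral. In step 5 it gives the ICT arm a false advantage of 14 points, more than LOCF at 0.3 to 0.6 does.

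**Conclusion.** The point holds. As written, the missing-data rule does not determine the primary status of a patient without week-12 records: it is inapplicable or yields failure at composite level, and can yield success by construction at the level of home records. Up to about 10 of 48 per arm are exposed through dropout, on the assumption that all of the planned 20% occurs before week 12. That is enough to change the primary conclusion in extreme configurations. The direction of bias cannot be stated: it depends on the level of imputation, on the missingness in each arm and on the carried-forward success rate, and the article fixes none of these. Unequal missingness is possible given the ICT-only educator follow-up, but is not established.

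**What to change.** 1. Remove LOCF for the primary outcome. Analyse all randomised patients, and count a patient whose week-12 records do not show every applicable criterion met as not having reached the optimal dose.
2. Because that coding can favour the arm with better recording, prespecify multiple imputation by arm and a tipping-point analysis as sensitivity analyses, and report missing week-12 data by arm.
3. Restate the power: about 75% at 48 per arm if 88% and 55% are completer rates and 20% per arm are coded as failures. If those rates were meant to count dropouts as failures already, say so; this loss then does not arise.
4. As a secondary improvement, replace LOCF for the continuous week-12 and week-24 outcomes with a likelihood-based repeated-measures model.

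Items 1, 2 and 4 are wording changes in the protocol and analysis plan and need no new data collection. Since the trial is open-label, they should be fixed before outcomes are examined by arm. The real cost is item 3: the sponsor must either accept the lower stated power or reconsider the sample size.

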### Study design

This is a 24-week, open-label, randomized, multi-center ICT-based clinical trial conducted in two different university-affiliated hospitals, Samsung Medical Center and Samsung Changwon Hospital. There are three follow-up measures: baseline, post-intervention at week 12, and at week 24. Subjects diagnosed as T1DM, T2DM, and/or post-transplant DM who are initiating basal insulin or intensifying their insulin regimen to a basal-bolus regimen will be given education on insulin injection, dose adjustment, and prevention of hypoglycemia and will be provided a Bluetooth-enabled glucometer at visit 1 for screening. Subjects will receive instructions to measure daily glucose level using a home glucometer, to record insulin regimen and dose, complete the hypoglycemia diary in the application if blood glucose <70 mg/dL or a hypoglycemic event occurs, and to synchronize data so it automatically transfers to the system. Subjects who synchronized their information daily during a 1-week run-in period will be accepted into the clinical trial and randomly assigned to either the ICT-based intervention group or the conventional intervention group at a ratio of 1:1. After randomization during week 1, telephone counselling will be provided for re-instructing insulin dose adjustment and re-confirming participants’ use of the at-home measurement device and PHR applications (visit 2; televisit). Subjects in the ICT-based intervention group will receive algorithm-based feedback messages when their glucose levels are out of the target range, in addition to recording, saving, and sending their data to the server via PHR applications. Subjects in the conventional intervention group will only record, save, and send their data to the server via PHR applications, without feedback messages. Investigators will examine the saved health information, including level of blood glucose, insulin dose, details on hypoglycemia recorded in the hypoglycemia diary, food diary, and number of steps, transferred through the PHR applications. At each clinical visit, anthropometric parameters, current medication use including insulin dose and other glucose-lowering agents, vital signs, body composition, and a questionnaire assessing satisfaction with the investigation will be examined, and blood tests will be performed. Figure 1 shows an overview of the study.

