### Education on insulin injection, dose titration, and prevention of hypoglycemia

At the screening visit (visit 1), all subjects are given face-to-face education on insulin injection, dose titration, and prevention of hypoglycemia. The initial daily basal insulin dose will be 10 units per day or 0.1–0.2 units per kg of body weight. The initial daily basal insulin dose can be increased when the fasting blood glucose level is 250 mg/dL or more at initiation, but it should not exceed 0.3 units per kg per day. The initial pre-prandial rapid-acting insulin dose will be 4 units or 0.1 unit per kg or 10% of the basal insulin dose. For patients who have already used insulin before enrollment, they will start on their previous insulin dose and adjust from there. Subjects in the study are instructed to titrate their insulin dose based on the glycemic target of fasting glucose 80–130 mg/dL in the morning, for those who are under 65 years of age and do not have a history of severe hypoglycemia that cannot be recovered without help. The target of fasting glucose level 100–140 mg/dL in the morning will be applied for subjects with 1) history of severe hypoglycemia; 2) age ≥ 65 years; 3) duration of diabetes mellitus over 15 years; 4) decreased renal function (estimated glomerular filtration rate < 45 mL/min/1.73 m^2^); 5) BMI <18.5 kg/m^2^; 6) unawareness of hypoglycemia; 7) unpredictable changes in blood glucose level; and 8) difficulties understanding the education provided.

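### With clinic measurements only at baseline, week 12 and week 24, blanket LOCF would enter the pre-randomisation value as the result of every early dropout for the continuous clinic-measured secondary outcomes

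*Protocol article*

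**What the plan says.** The Data analysis section states: "For handling missing data, last-observation-carried-forward (LOCF) imputation method would be performed". It is the only missing-data method given, and it is not limited to particular outcomes or visits. The same section compares continuous secondary outcomes by Student's t-test or Wilcoxon's rank-sum test.

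The measurement schedule is sparse. The Study design section says: "There are three follow-up measures: baseline, post-intervention at week 12, and at week 24". Under Laboratory tests: "At visits 1, 3, and 4, blood samples are collected after at least 8 h of fasting". Under Anthropometric and vital sign measurements: "At visits 1, 3, and 4, height, body weight, blood pressure, and pulse will be measured"; body composition is covered in the same section. The status version of the Diabetes Treatment Satisfaction Questionnaire (DTSQs) is also given at visits 1, 3 and 4. Visit 3 is the week 12 visit, since the primary outcome window is "during week 12 (last 7 days prior to visit 3").

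Visit 2 supplies no clinic measurement. It is a telephone contact for re-instruction and for "re-confirming participants’ use of the at-home measurement device and PHR applications (visit 2; televisit"). Visit 1 precedes the run-in and randomisation: "At the screening visit (visit 1), all subjects are given face-to-face education on insulin injection, dose titration, and prevention of hypoglycemia".

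The Sample size section raises recruitment to 48 per group "to allow for a dropout rate of 20% during follow-up". The section on discontinuation describes compiling results up to the time of leaving and mentions no further measurement.

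**The concern.** LOCF does least harm when values are stable and visits are frequent. Neither holds here. Subjects enter with HbA1c of at least 8.0% while starting or intensifying insulin, so HbA1c should fall in both arms, and nothing is measured in clinic between visit 1 and week 12. Applied as written, the rule gives every subject lost before week 12 a change of exactly zero, at week 12 and again at week 24. A subject lost later has the week 12 value repeated at week 24. The filled-in values then enter the t-test or rank-sum test as if observed.

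HbA1c at weeks 12 and 24 is a named secondary outcome and part of the secondary hypothesis. At stake is whether its reported between-arm difference reflects treatment or the pattern of dropout. Unequal dropout is possible: the trial is open-label, and educator-initiated calls after feedback messages are described only for the ICT arm.

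**Working it through.** **The plan's own figures.** With 55% v 88%, two-sided alpha 0.05, 90% power and pooled variance:

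n = [1.960 x sqrt(2 x 0.715 x 0.285) + 1.282 x sqrt(0.55 x 0.45 + 0.88 x 0.12)]^2 / 0.33^2 = 37.2, so 38 per group. Then 38 / (1 - 0.20) = 47.5, so 48 per group.

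Both stated figures reproduce. Twenty per cent of 48 is 9.6, so about 10 subjects per arm could have visit 1 carried forward. This is an upper bound, because it puts all dropout before week 12.

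**Formula.** Let mI and mC be the true mean changes (intervention, control) and dI and dC the shares lost before week 12. Assume that dropouts would have changed as completers do. LOCF sets their change to zero, so

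LOCF difference = mI(1 - dI) - mC(1 - dC).

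- Equal dropout d: (mI - mC)(1 - d). A true difference shrinks by the fraction d; a null difference stays at zero.
- No true effect, common fall f: the false difference is -f(dC - dI).

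**Numbers from the formula.** The documents give no HbA1c change, so the changes below are assumptions. Dropout is intervention / control.

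| True changes | True difference | 20% / 20% | 10% / 30% | 30% / 10% |
|---|---|---|---|---|
| -1.5, -1.0 | -0.50 | -0.40 | -0.65 | -0.15 |
| -2.0, -1.5 | -0.50 | -0.40 | -0.75 | -0.05 |
| -1.5, -1.5 | 0.00 | 0.00 | -0.30 | +0.30 |

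A smaller true effect can change sign. With changes -1.7 and -1.5 (difference -0.20) and 30% / 10% dropout: -1.7 x 0.7 + 1.5 x 0.9 = -1.19 + 1.35 = +0.16.

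**Error rate and power by simulation.** All inputs except the 48 per arm and the floor of 8 are assumptions: baseline HbA1c mean 9.5%, SD 1.2, floor 8; mean fall 1.7; residual SD 1.0; baseline slope 0.5; all modelled dropout before week 12 and at random within arm.

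No true effect, LOCF t-test:

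| Early dropout (intervention v control) | Gap x fall | False positives |
|---|---|---|
| 20% v 20% | 0 | 5% |
| 5% v 10% | 0.05 x 1.7 = 0.09 | about 6% |
| 10% v 20% | 0.10 x 1.7 = 0.17 | about 10% |
| 10% v 30% | 0.20 x 1.7 = 0.34 | about 23-26% |

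In these null scenarios, baseline-adjusted analysis of the observed values gives a difference of about 0.00 and about 5% rejection. With mean falls of 1.0 to 2.5 points, the 10% v 30% false difference runs from about -0.2 to -0.5.

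True effect -0.6, 20% early dropout in both arms. LOCF estimates -0.6 x 0.8 = -0.48.

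| Analysis | LOCF | Observed values |
|---|---|---|
| t-test | about 39% power | about 64% power |
| Baseline-adjusted | about 47% power | about 73% power |

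Comparing like with like, the power lost to LOCF is about 25 points (64 - 39) for the t-test and about 26 (73 - 47) with adjustment. Setting 39% against 73% would also count the gain from baseline adjustment. With 10% early dropout in both arms, t-test power is about 53% under LOCF against about 70% on observed values.

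**The case against.** The strongest objections are these.

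- *The article does not say that a pre-randomisation value may be carried.* If the analysis set required a post-baseline value, visit 1 would never be imputed. That restriction may exist in a fuller document, but the rule as printed has no such limit. The concern therefore stands as what follows from the text as written.
- *Unequal dropout is assumed.* The only dropout figure is 20% over the whole follow-up, with no split by arm or time, and the run-in already removes subjects who do not transfer data. This stands, and it limits the size: at 5% v 10% early loss the error rate is close to nominal. A reader might infer that only the ICT arm is followed up and so must retain more subjects. The documents do not support that. Both arms receive the week 1 call, may telephone the educator and have synchronisation checked before weeks 12 and 24. The direction of any imbalance is open.
- *The advantage of observed-data analysis is built in.* The comparison lets dropouts improve as completers do. If they instead stay near baseline, LOCF recovers the all-patient difference (about -0.47 in both) and the observed-data analysis overstates it (-0.60). This stands, and it is a reason for a sensitivity analysis. It does not justify assuming no change for every dropout as the main analysis.
- *The outcomes are secondary.* This stands and sets the grade.

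**Conclusion.** The concern holds for the continuous secondary outcomes measured only in clinic: HbA1c, lipids, weight, blood pressure, body composition and DTSQs. As written, LOCF would give early dropouts their pre-randomisation value at weeks 12 and 24. For HbA1c, equal early dropout shrinks a true difference by about the dropout fraction and costs power; with no true effect it causes no bias. Unequal dropout can create, inflate or reverse a difference by about the dropout gap times the mean fall. That is from about 0.09 to 0.34 points across the null scenarios shown, conditional on the assumed 1.7-point fall.

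A reader might infer that LOCF biases all the secondary comparisons, or undermines the trial's main result. The documents do not support either. The primary outcome and the sample size are outside the point. Step counts, home glucose and app-recorded insulin doses arrive between visits, so LOCF need not return baseline for them. For HbA1c below 7%, entry at 8.0% or more means that a carried baseline acts almost as non-responder imputation, which is easier to defend. "Before randomisation" is also the exact description of the visit 1 value; "before titration" is only approximate, as regimens may have begun up to a month before participation. Grade: should-fix.

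**What to change.** In the Data analysis section, replace LOCF for the continuous clinic-measured secondary outcomes by a mixed model for repeated measures on all observed week 12 and week 24 values. Include arm, visit, arm by visit, baseline and the two randomisation factors (institution, and pre-prandial insulin two or more times per day), with no imputation. Keep LOCF as a sensitivity analysis, and add one in which dropouts stay near baseline, since the mixed model assumes missing at random.

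The change needs no new data and should be made before outcome data are seen. Its cost is that a model replaces the simple t-test or rank-sum test for these outcomes, and that the result rests on the missing-at-random assumption. Limiting carry-forward to post-baseline values would be a smaller edit and would remove the baseline problem, but it would still repeat week 12 values at week 24.
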